### Secondary Outcomes: Plasma-Based Biomarkers of Amyloid and Tau

Blood draws are scheduled during the behavioral session. At each time point, we will collect 20 mL of blood (15 mL for plasma and 5 mL for serum). Following standard operating procedures, blood will be drawn via venipuncture from each participant into one 10 mL and one 5 mL lavender-top ethylenediaminetetraacetic acid tubes and one 5 mL red-top serum tube. Immediately after collecting blood, each ethylenediaminetetraacetic acid tube will be gently mixed by inverting 8 to 10 times to ensure proper mixing of blood and anticoagulant and kept at 4 °C. The red-top tube will also be gently mixed by inverting it 5 times and placed upright at room temperature for 30 minutes to allow for complete clot formation. Furthermore, within 24 hours of acquisition, all samples will be centrifuged for 10 minutes at 2000×*g* at 4 °C, and one-third of the aliquots will be shipped to our collaborators at the University of California, Irvine, for analysis. In this study, the secondary outcome variables are the plasma Aβ_42_/Aβ_40_ ratio, used to quantify amyloid pathology, and plasma p-tau217, used to determine tau pathology. Plasma samples will be analyzed using the automated Single Molecule Array (Simoa) HD-X analyzer with commercially available kits from Quanterix. A total of 100 µL of plasma will be used for the tau assays (p-tau217), and an additional 100 µL will be used for the 4-Plex panel.

### Other Outcomes

#### Behavioral and Imaging Measures of Sustained Attention and Mind-Wandering

##### Overview

Laboratory-based assessments of sustained attention and mind-wandering will include 2 behavioral tasks—the Shapes Expectation task [64,65], designed to place minimal demands on the participants, and the Go/No-Go task, a standardized task of sustained attention with embedded thought probes assessing mind-wandering. Participants will additionally complete the Gradual-Onset Continuous Performance Task in the MRI scanner.

##### Shapes Expectation Task

In this low-effort task, participants will simply be asked to focus on brightly colored geometric shapes on a computer screen. They will not be asked to remember the stimuli or respond to them. Following the presentation of the stimulus, a thought probe will appear on the screen instructing participants to report on the content of the thoughts they experienced while viewing the shape. This “thinking-aloud” technique in the context of a low-effort perceptual task has been shown to elicit a wide range of task-unrelated thoughts as well as to engage the activity of the 2 canonical networks critically implicated in mind-wandering—the default mode and the frontoparietal networks [64,65]. Participants will be provided with training examples before the commencement of the task. There will be a total of 9 trials with trials being of a short duration (≤20 s), a medium duration (30‐60 s), and a long duration (≥90 s). There will be no time limit imposed for the thought probes, and all responses will be recorded via a dictaphone.

##### Go/No-Go Task

In this task, participants will be presented with one of 2 visual stimuli (“X” and “M” or “Z” and “/”) for 750 ms, followed by an intertrial interval of 750 ms. They will be asked to press the corresponding key on frequent Go trials and to withhold responses on the less frequent (occurring 10% of the time) No-Go trials, which will be signaled by an auditory tone. Participants will complete 6 blocks of this task, with each block containing 54 Go trials, 6 No-Go trials, and 3 mind-wandering probes, resulting in a total of 18 mind-wandering probes. The quasi-randomly presented mind-wandering probes will ask participants to respond to categorize their immediately preceding thought as (1) “on task”; (2) “thinking about performance on the task”; or (3) “thinking about personal worries, daydreaming, fantasizing, or just lost in thought.”

##### Gradual-Onset Continuous Performance Task

In the MRI scanner, participants view a sequence of gradually appearing mountains and city scenes. They are asked to respond to frequently occurring city scenes (~90%) but to withhold their responses to mountain scenes [66,67]. Scenes transition gradually over 800 ms, and each of the 2 runs includes 9 blocks of varying durations (short: 44 s, medium: 52 s, and long: 60 s). At the end of each block, following the last trial, the scene transitions into a scrambled image, after which 2 thought probes are presented: (1) “To what degree was your focus just on the task or on something else?” and (2) “To what degree were you aware of your focus?” For the first probe, participants respond on a graded scale ranging from only else to only task, and for the second probe, from unaware to aware.

### Ambulatory Assessment of Mind-Wandering and Cognitive Variability

In alignment with recent recommendations for EMA-based studies [68], this study will collect EMA data 5 times per day over a 5-day period using study-provided smartphones. These assessments will be conducted before and after training. Participants will be provided with study-specific Android smartphones equipped with the MetricWire platform for EMA data collection, and they will undergo individualized training on EMA procedures. This training will help ensure participants can readily use the study application, understand the different measurements fully, and respond accurately to the EMA probes. The EMA platform will be programmed to signal participants with an audible beep and a pop-up notification at semirandom intervals throughout the day, structured into 5 time bins across waking hours. Mobile-based cognitive assessments of processing speed, working memory, and inhibitory control will include 3 tasks taken from the Mobile Monitoring of Cognitive Change (M2C2) battery [69]. The cognitive tasks will be completed immediately after each EMA report of mind-wandering.

### Mind-Wandering Prompts

#### Overview

Consistent with current best practice in EMA mind-wandering research [68,70,71], each signal will prompt participants to provide information about mind-wandering and contextual details from the moment they were signaled. At each signal, participants will be presented with the following probes: (1) In the moments just before the notification, to what degree had your mind wandered to something other than what you were doing? (2) In the moments just before the notification, to what degree were you actively directing what was on your mind? (3) In the moments just before the notification, to what degree were you aware of what was on your mind? and (4) In the moments just before the notification, to what degree were your thoughts moving freely? For each of these prompts, responses will be collected on a 5-point Likert-type scale, ranging from not at all (0) to very much so (4), with intermediate options of a little, somewhat, and quite a bit. Our primary variable will be the overall rate of mind-wandering in daily life.

#### Symbol Search Task

This is a speeded performance task, measuring processing speed and attention. Participants will be presented with a set of 3 symbol pairs located on the upper half of the screen and 2 symbol pairs on the lower half of the screen. They are instructed to select which of the bottom symbol pairs matches 1 of the 3 symbol pairs above, as quickly and accurately as possible. A total of 20 trials with an intertrial interval of 200 ms will be administered, and each set of stimuli will be presented until the participant selects a response. The SD of response times will be computed, with higher scores reflecting higher processing speed variability.

#### Grid Memory Task

This task is a delayed short-term recall task and measures visual working memory abilities. First, participants complete a 3-second encoding phase in which they are presented with a 5×5 grid containing 3 red dots. Participants are instructed to remember the locations of the 3 red dots. Second, participants complete an 8-second distraction phase where they are presented with a 5×6 grid of “F” letters among an array of “E” letters and are directed to select all the “F” letters as quickly as possible. Finally, they complete a retrieval phase where they are presented with an empty 5×5 grid and must indicate the location of the 3 red dots; this grid will be displayed until the participant submits their selection. A total of 4 trials will be administered. The SD of the Euclidean distance of the location of the incorrect dot to the correct dot location will be computed, with higher scores indicating more variable placement.

#### Letter Go/No-Go Task

This task is a continuous performance task measuring attention and inhibitory control. Participants will be presented with a series of 30 letters, one at a time, and are instructed to tap a button as quickly as possible when they are presented with each letter. However, when the participant is presented with the letter “X,” they are instructed to withhold their response. Each letter will be presented for 1000 ms with an intertrial interval of 500 ms, and the ratio of Go/No-Go trials is 5:1.

### Data Management and Analysis

Our laboratory is dedicated to conducting rigorous and reproducible randomized clinical trials that evaluate the feasibility and efficacy of lifestyle-based psychosocial interventions. We have established detailed procedures for data collection, reduction, storage, and analysis, and these protocols will be followed in this study.

All data collected as part of this study, including behavioral, self-report, and neuroimaging data, will be stored in the PI’s laboratory, accessible only to authorized laboratory personnel. Blood samples will be stored at the Clinical Research Center, and deidentified EMA data will be housed on MetricWire’s secure cloud server. For screening and behavioral assessments, 2 independent raters will code the measures (either manually or via custom scripts), with a third rater confirming agreement. Questionnaire data will be coded using custom scripts that have been independently reviewed by 2 laboratory members and validated against manual coding. EMA data will be processed using tools provided by MetricWire and subsequently analyzed with custom scripts.

Structural MRI and functional MRI (fMRI) preprocessing will be performed using the standardized fMRIPrep (version 1.4.1) pipeline [72]. T1-weighted (T1w) images will be corrected for intensity nonuniformity [73], skull-stripped (with brain surfaces reconstructed using FreeSurfer, version 6.0.1) [74], and spatially normalized to the Montreal Neurological Institute (MNI) space through nonlinear registration [75]. Functional data will be corrected for susceptibility distortion [76] and motion [77] and co-registered to the T1w using boundary-based registration [78]. Motion-correcting transformations, BOLD-to-T1w transformations, and T1w-to-template (MNI) warps will be concatenated and applied in a single step using Lanczos interpolation (ANTs, version 2.1.0). Physiological regressors [79], framewise displacement [80], and global signal will be extracted from the fMRI data. Preprocessed fMRI data will then be denoised using the signal clean function within Nilearn [81]. Potentially confounding sources of signal variance will be removed: mean CSF, white matter, global signal, a 24-parameter motion model, and the linear trend. To further control for motion-related confounds, we will add a spike regressor for each frame with a framewise displacement of ≥0.5 mm [80]. A high-pass temporal filtering at 0.01 Hz will also be applied.

Preprocessed fMRI data will then be parcellated using the Glasser functional atlas with 360 cortical regions and 19 subcortical regions [82,83]. The functional atlas will be transformed from MNI space to each participant’s native space. We will then extract the BOLD signal time courses from each of the 379 regions by averaging the signal across all voxels within each region. To compute the statistical dependence between BOLD signal across 2 nodes, we will first z-score each time series, compute their element-wise product, and then average this product to obtain the Pearson correlation coefficient between each pair of nodes. Calculating the Pearson correlation for all pairs of nodes will result in a 379×379 functional connectivity matrix for each participant, which will be used to compute the DMN connectivity.

Following the preprocessing of self-report, behavioral, and neuroimaging data, analyses will be conducted to determine intervention feasibility and acceptability. For preliminary effects on plasma biomarkers of AD pathology, behavioral and neural metrics of mind-wandering, and other secondary outcomes, we will fit linear mixed models to account for within-subject correlations arising from measuring each subject at 2 time points. In these models, emphasis will be placed on estimating effect sizes and CIs, rather than on hypothesis testing. As we are including adults with SCD based on self-reported concerns, we will also conduct sensitivity analyses using the total score on the Penn State Worry Questionnaire [58] to examine whether feasibility, acceptability, and preliminary effects differ as a function of worry scores within the current sample.

### Adverse Event Reporting

Adverse events (AEs) during the clinical trial will be reported in accordance with a detailed protocol developed in alignment with the NIH Adverse Event Reporting Guidelines. Any event brought to the study team’s attention will be immediately reported to the study PI and the clinical trial safety monitor. The safety monitor, a cognitive neurologist with extensive expertise in neurocognitive disorders, will evaluate the event and determine its relationship to the study. Each event will be classified as unrelated, possibly related, probably related, or definitely related using standard criteria for clinical trials.

For all events deemed possibly, probably, or definitely related to the study, they will then be categorized by severity as (1) mild AE—does not require treatment; (2) moderate AE—resolved with treatment; (3) severe AE—inability to carry on normal activities and requires professional medical attention; (4) life-threatening or disabling AE; and (5) fatal AE. For mild AEs, we will document the event, and the study team will determine whether changes to the study procedures are warranted. For moderate or more severe events that are related to the study, a detailed report will be prepared and submitted to the institutional review board (IRB) and the NIH Program Officer assigned to the study. If 2 participants experience the same AE, recruitment will be stopped, a report will be submitted to the IRB and NIH, and any revisions to the study protocol suggested by either the IRB or the NIH will be implemented. In addition, annual reports to the IRB and progress reports to the NIH will be submitted, including information on enrollments, withdrawals, completions, and the occurrence of AE.

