### Study Procedures

Participants who meet the demographic criteria, along with criteria for the ECog Questionnaire, the T-MOCA, the IADL questionnaire, and MRI safety, are invited to the Clinical Neuroscience Laboratory at The Ohio State University for an initial in-person screening session. At this visit, visual acuity is assessed using the Snellen chart, and a blinded research assistant administers the UDS3-NB.

Participants meeting criteria for intact objective cognitive performance are then invited to a behavioral testing session at the Clinical Neuroscience Lab and a neuroimaging session at the Center for Cognitive and Behavioral Brain Imaging. During the behavioral session, a trained nurse from the Clinical Research Center at The Ohio State University collects the blood plasma sample, after which participants complete 2 behavioral measures of sustained attention and mind-wandering. As psychoaffective factors can influence perceived ratings of SCD, participants also complete a battery of questionnaires assessing stress (the Perceived Stress Scale [55]), depression (the Center for Epidemiologic Studies Depression Scale [56]), anxiety (the Beck Anxiety Inventory [57]), worry (the Penn State Worry Questionnaire [58]), quality of life (the World Health Organization Quality of Life–Brief [59]), and perceived racial discrimination (the Everyday Discrimination Scale [60]). We also administer the Motivation to Change Lifestyle and Health Behaviors for Dementia Risk Reduction [61] to quantify psychological and cognitive factors that influence engaging in health behaviors.

At the same session, participants receive training on EMA procedures and are provided with study-specific smartphones (Samsung Galaxy phones) to collect EMA data on mind-wandering, cognitive functioning, perceived stress, affect, and arousal for 5 days between sessions. Finally, structural and functional MRI data are collected at the neuroimaging session to quantify changes in the integrity of the DMN.

After completion of all assessment sessions, participants are randomized to either the iMBSR or the iLifeEd group with a 1:1 allocation ratio. All assessments will be readministered immediately following the 8-week intervention.

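### Adverse events are graded for severity only if first judged related to the study, so events judged unrelated carry no grade and all-cause events cannot be compared between arms by grade

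*Protocol article*

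**What the plan says.** The Adverse Event Reporting section of the protocol article sets out an order of steps.

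- **Capture.** "Any event brought to the study team’s attention will be immediately reported to the study PI and the clinical trial safety monitor".
- **Causality.** The safety monitor "will evaluate the event and determine its relationship to the study". There are four categories: "Each event will be classified as unrelated, possibly related, probably related, or definitely related using standard criteria for clinical trials".
- **Severity.** "For all events deemed possibly, probably, or definitely related to the study, they will then be categorized by severity as" mild, moderate, severe, life-threatening or disabling, or fatal.
- **Event-level report.** "For moderate or more severe events that are related to the study, a detailed report will be prepared and submitted" to the IRB and the NIH program officer.
- **Repeat events.** "If 2 participants experience the same AE, recruitment will be stopped", and a report goes to the IRB and NIH. No relatedness or severity condition is attached.
- **Periodic reports.** Annual IRB reports and NIH progress reports are filed, "including information on enrollments, withdrawals, completions, and the occurrence of AE".

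The section also says that reporting follows a detailed adverse event protocol, which is not shown.

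On timing, the Study Procedures section says: "After completion of all assessment sessions, participants are randomized to either the iMBSR or the iLifeEd group". The baseline blood draw and MRI therefore come before allocation. All assessments are repeated right after the 8 weeks.

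**The concern.** How bad an event was and what caused it are two different questions. The section answers the second first and asks the first only when the answer is some degree of related. Whether a severity grade exists then depends on one person's causal opinion.

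That opinion is hard to form here. Participants are aged 50 or older and follow an asynchronous online program for 8 weeks. Intercurrent illness and effects of the program, such as distress, may not be easy to tell apart.

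Randomization protects the comparison of all events that start after allocation. A comparison limited to events judged related depends on attribution as well. If grades exist only for related events, the comparison by grade that rests on randomization alone is not available from the data collected.

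The Study Design section lists potential safety issues among the things a pilot study helps to assess before a large trial. The grading rule works against that purpose.

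**Working it through.** No figure in the article bears on this point, so there is nothing to reproduce numerically. The check follows an event through the described steps and asks what data exist at the end.

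**1. Cells that the flow can fill.** There are four relatedness categories and five severity grades. Full recording gives 4 × 5 = 20 combinations. The described flow grades the three related categories only, which gives 3 × 5 = 15 combinations plus one undivided group of unrelated events. The five grades within that group are not recorded.

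**2. What this does to a comparison between arms.** For arm *a*, let S_a be the number of related events graded severe or worse, and U_a the number of events judged unrelated, counting only events with onset after randomization. The flow yields S_a and U_a, but not how many of the U_a were severe or worse. So:

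- The all-cause count of severe-or-worse events in arm *a* lies anywhere from S_a to S_a + U_a.
- The difference, iMBSR minus iLifeEd, lies anywhere from S_1 − S_2 − U_2 to S_1 − S_2 + U_1.
- The width of that interval is U_1 + U_2, the total number of unrelated events in both arms.

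The uncertainty grows with each event judged unrelated. Some of it could be removed by going back to the records; a death, for example, is recognizable without a formal grade. But the described steps do not supply the grades.

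**3. Whether another step restores the grade.** Three other steps reach unrelated events, and none assigns a grade. Capture sends every event to the principal investigator and the monitor. The periodic reports promise occurrence only. The repeat-event rule acts on the same event in two participants whatever its cause or severity, and it triggers a report without mentioning a grade.

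**4. What relatedness refers to.** The monitor judges relatedness to the study as a whole. That covers the two programs and also the blood draws, MRI, EMA and testing. For baseline events the date settles the matter, because no program has yet been assigned. At the post-intervention visit it does not: a reaction to the blood draw and a reaction to the program could both be labelled definitely related, with nothing on the stated scale to tell them apart.

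**The case against.** The strongest reply is that this is a journal article, that it cites a detailed adverse event protocol, and that form fields and tabulations are commonly left to such a document. This stands for the absence of a tabulation plan and largely for the lack of a split between program and procedure, which is why that split is only a secondary step here. It does not answer the main point. The article does not merely leave grading out; it states a condition for grading. Either that is the operating rule or the article misdescribes it, and a correction is due in both cases.

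It can also be said that the trial is a Stage I feasibility study with 30 per arm and sets no between-arm safety comparison as an objective, and that unrelated events could be graded later from the records. Both are fair and limit the weight of the point. The second also shows how easily it is repaired.

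The safety monitor is not among the people listed as unblinded in the Randomization and Blinding section, so nothing shows that relatedness is judged with knowledge of the arm. That reduces the worry about biased attribution but leaves the missing grades as they are.

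Two stronger readings are tempting, and the document does not support either.

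- A reader might infer that reactions to the baseline blood draw or MRI are pooled with harms of the programs. No pooling rule is stated, and because randomization follows all baseline sessions, dates separate those events.
- A reader might infer that unrelated severe events escape the IRB and NIH except through periodic reports. The repeat-event rule contradicts this, since it triggers a report with no relatedness condition.

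**Conclusion.** The point holds as a defect in a stated rule. Under the Adverse Event Reporting section as written, events judged unrelated have no severity grade even if severe, and all-cause events cannot be compared between arms by grade from the data the described flow produces.

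The size cannot be given as a number, because the article reports no adverse event counts and no expected rates. In kind, the gap covers every event judged unrelated, in both arms. Ungraded does not mean unrecorded or unreviewed.

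The conclusion assumes that the described order of steps is the operating one. If the detailed adverse event protocol already grades every event, only the article's wording needs correcting. Whether the triggers for reports to the IRB and NIH should differ cannot be settled without that protocol, and the two documents should be reconciled on it.

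**What to change.** **Main change.** Grade every adverse event for severity independently of its relatedness, including retrospectively for events already recorded. Tabulate all events with onset after randomization by arm and grade, with relatedness as a separate column.

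**Secondary step.** Record relatedness separately to the assigned program and to assessment procedures, since date alone cannot separate these at the post-intervention visit.

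**Reconciliation.** Check the article's wording on grading and reporting against the detailed adverse event protocol and make the two agree. No change to the reporting triggers is proposed here.

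**Cost.** Slightly more work on the adverse event form, plus a second look at events already on record. Every event already reaches the principal investigator and the safety monitor, so no new data stream is needed, and no visit, program content or endpoint changes. The timing is workable: the Results section reports 31 of 60 participants randomized by December 1, 2025, which left 60 − 31 = 29 to come at that date.
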